### Study intervention

The FACE app is based on a transdiagnostic model of mechanisms linking childhood trauma to psychopathology and addresses the thematic components Self- and Emotion Regulation (SER) and Social Skills and Social Information Processing (SSIP) for the promotion of resilience and well-being. It was developed based on well-established cognitive-behavioural principles that have been used in other web-based self-help apps [13] and offers psychoeducative materials and exercises in various formats (text, audio, video).

In addition to two components SER and SSIP (see Fig. 1), there are two additional parts intended to frame the user’s experience: an introduction and a conclusion/farewell. First, the general introduction, available to everyone from the start, explains the app interface, presents general information on ACE (psychoeducation about prevalence, types, and consequences), and encourages reflection on one’s personal status and resources plus the formulation of personal goals for the app. Towards the end of the intervention, the conclusion/farewell encourages the revisiting of the goals and ideas of the start and the reflection on what was most helpful while using the app. In addition, a collection of short activities and exercises relevant to everyday life and promoting physical and mental well-being is accessible as a toolbox at all times, but also referred to at relevant moments throughout the rest of the content.

Within each of the two thematic components SER and SSIP, four different modules include informational reading on ACE and ACE-related topics, as well as prompts for participants to actively reflect on what was learned in the readings and exercises to apply their knowledge and practice skills (see Table 1). The first module includes information about ACE in relationship with SER or SSIP respectively. Modules 2 and 3 contain information about the theoretical background of SER or SSIP respectively as well as information, writing tasks and exercises on the modification of possible cognitive biases. In module 4, the focus is on learning new skills and their implementation/transfer in daily life. Participants are encouraged to work through one module per week and to complete the exercises, which adds up to approximately one hour of engagement with the app per week.

**Table 1 Tab1:** Outline of the components of the FACE self-help app

	**Introduction module** (always available) - Explanation of how the app works - Formulation of personal goals - Psychoeducation on prevalence, types, and consequences of ACE - Contact information on where to find additional help	
	**Toolbox with short exercises for daily life** Exercises and suggestions connected to - emotion regulation, i.e. to distraction, relaxation, encouragement, perspective and enjoyable activities (SER component) - social relationships, i.e. to personal boundaries, feeling at ease before, during and after social situations, social challenges and enjoyable activities (SSIP component)	
**Thematic Modules**	**SER Component**	**SSIP Component**
1. Psychoeducation and personal relevance of topics	- Importance of emotions for one’s life, thoughts, and behaviour - Emotion regulation and ACE	- Importance of relationships and reflection on status quo of personal relationships - Relationships and ACE
2. Promoting behavioural skills	- Emphasis on the active influencing of situations, behaviour and feelings to minimise negative and push positive emotions	- Emphasis on the identification and active promotion of social skills
3. Identification and resolving of dysfunctional cognitive patterns	- Identification of biased automatic perception and thought patterns, and how to counter them	- Identification of biased expectations towards social situations and interpretations of other people’s behaviour, and how to counter them
4. Promoting skills and long-term improvement	- Problem solving and the creation of favourable conditions for one’s emotional experience	- Dealing with difficult social situations and the building of positive social experiences - Learning to play to one’s social strengths
	**Final module/Farewell** - Summary and reflection of what has been learnt - Reiteration of contact information to find additional help - Tips on how to continue	

The FACE app was developed in an iterative co-design with emerging adults to deliver relevant interventions in an attractive, easy-to-use and low-threshold framework adapted for the target group. First, interviews with 29 emerging adults with a history of ACE were conducted to determine their expectations of a digital self-help intervention. Two focus groups accompanied in the development of the content of the app which included psychoeducative materials and exercises in various formats (text, audio, video). The app adapted content of different existing web-based self-help interventions such as the ECoWeb app for addressing social cognition and emotion regulation [67, 68], the SOLUS program for addressing loneliness and social activities [69], the HERMES program for problem-solving [70], the LEAVES program for emotion regulation, social relationships, and activities [71] and the REMOTION program for emotion regulation [72, 73]. The FACE app will be implemented as a progressive web app (PWA) and participants can access the PWA either from their smartphone or from regular internet browsers through a secure website, using a password-protected personal account.

#### Participants’ support and guidance

During the 10 weeks of the use of the FACE self-help programme, participants will receive weekly written feedback and support via an integrated messenger function - either from a psychologist or social worker of the School of Social Work at the University of Applied Sciences and Arts Northwestern Switzerland or from trained and supervised master students in Clinical Psychology of the University of Bern. This weekly support, which was short but individualised in terms of progress and focus, acknowledges and motivates participants in their engagement with the app, keeping emphasis on positive reassurance. It aims to improve adherence, provides a weekly structure, support for technical problems and the possibility to ask further questions. If needed, stabilising interventions via phone calls are offered by a psychologist within the FACE team who can also, if needed, provide support with seeking more comprehensive treatment through counselling services, psychotherapists or psychiatrists close to where the participants live. Reports of adverse events and negative effects will be collected.

### Statistical analyses

Analyses will be conducted according to the intention-to-treat paradigm. Additionally, we will conduct per-protocol analyses, including participants who complete baseline and post-intervention assessments and log into at least four modules defined as minimal therapeutic exposure. The significance level will be two-sided at *p* ≤ 0.05. To test the efficacy of the intervention in the intervention group compared to the control group, we will use linear mixed models. The differential effects of the SER and SSIP components will then be tested with interactions between the component and time. These analyses will model random slopes and intercepts for participants, test the fixed effects of the condition, as well as repeated assessments over time, using data from all participants. Linear mixed models have the advantage that they can account for missing values through maximum likelihood estimation [74]. Cohen’s d and f will be calculated as effect sizes. Furthermore, we will calculate Reliable Change Indexes [75].

Potential predictors and moderators of intervention outcome, such as gender or ACE severity will be analysed using multiple linear regressions. To analyse the mediation hypotheses and the longitudinal interplay of the variables, we will conduct path and structural equation analyses. Analyses will be conducted in SPSS, R and Mplus. There are no statistical stopping rules in this trial.

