### Secondary objectives

The secondary goals of this study are.

1) to test the efficacy of the FACE self-help app in improving self-efficacy for managing emotions and problem-solving as facets of self- and emotion regulation, fear of negative evaluation and social avoidance as facets of social skills and social information processing, as well as self-esteem (secondary outcomes).

2) to test the differential effects of the self- and emotion regulation (SER) and the social skills and social information processing (SSIP) components on all outcomes. We hypothesize that SER will specifically improve self-efficacy for managing emotions and problem-solving and thus will have a greater effect on these variables than will SSIP. Similarly, we expect that SSIP will specifically improve fear of negative evaluation and social avoidance and thus will have a greater effect on these variables than will SER.

3) We aim to analyse the effects of the FACE self-help app on real-life ecological momentary assessment data in affective states, distress in several areas of life, social interactions, the use of coping strategies and resilience. We expect that the FACE self-help app will improve these variables compared to the waiting list control group.

4) Finally, we assess the degree of satisfaction of the participants with the FACE self-help app.

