#### Sample size calculations

*Main effects*: We expect a moderate effect size of *f* > 0.25 for the comparison of the intervention and the waiting list control group and a small effect of *f* > 0.10 for the differential effects between SER and SSIP. Based on previous studies on web-based self-help interventions, we expect a correlation between the pre- and post-measurement of *r* = 0.6. Power analyses were conducted using G*Power [76] with a power of 0.8, an alpha error of 0.05. With three measurements, a sample size of 24 is required to detect a within-between interaction between the active intervention and the waitlist control group. A sample size of 162 is required to detect a small effect between the two active conditions and the waitlist control group.

*Intensive longitudinal data analysis*: Furthermore, the study combines data from the EMA with survey data in a multi-level model to investigate mechanisms and moderators of changes in well-being and resilience in the participants over the course of the study. Structural equation models including mediation analyses require a minimum sample of 241 for detecting a moderate effect (four latent and 25 observed variables [77]). This sample size will also allow accurate estimates of the regression coefficients, variance components and standard errors for multilevel analyses of the EMA data [78]. Sample size required for intensive longitudinal analysis is still a subject of ongoing research and it depends largely on (a) the effect size, (b) the number of measurements, and (c) the proportion of measures answered each day. Consequently, we aim to randomize up to 250 participants.

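### The SER-versus-SSIP contrast is not defined, and the 162 given for it is a three-group interaction that the app effect alone can make significant

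*Protocol article*

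**What the plan says.** **Secondary objectives.** The question is head-to-head and directional. For self-efficacy for managing emotions and for problem-solving, SER is expected to improve scores and "thus will have a greater effect on these variables than will SSIP". The reverse is expected for fear of negative evaluation and social avoidance. The Trial design section describes the component comparison as a crossover.

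**Statistical analyses.** After a sentence on app versus control, the text reads: "The differential effects of the SER and SSIP components will then be tested with interactions between the component and time". It adds that these analyses "test the fixed effects of the condition, as well as repeated assessments over time, using data from all participants". It does not say how component is coded, what value a waiting-list participant takes, or which contrast carries the conclusion.

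**Sample size calculations.** The effect assumed for this objective is "a small effect of *f* > 0.10 for the differential effects between SER and SSIP". The sample size attached to the small effect is worded differently: "A sample size of 162 is required to detect a small effect between the two active conditions and the waitlist control group".

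**The concern.** The effect size is labelled as SER versus SSIP, but the sample size belongs to a comparison of three groups, one of which receives no app. The two have different null hypotheses. A three-group interaction with time has as its null that no group changes differently from any other. That null is false once either active group improves over the waiting list, which is what the primary hypothesis predicts.

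If that interaction is the test behind objective 2, a significant result could be read as a difference between components when it reflects only that the app works. The objective covers all outcomes, so the same misreading could recur on each of them. It would also be most likely when the app is most effective.

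**Working it through.** **Inputs from Sample size calculations.** App versus waiting list: "We expect a moderate effect size of *f* > 0.25 for the comparison of the intervention and the waiting list control group". SER versus SSIP: f = 0.10. Correlation: "we expect a correlation between the pre- and post-measurement of *r* = 0.6". Three measurements, power 0.80, alpha 0.05. From Trial design: control to intervention 1:2. Up to 250 are randomised. My assumptions: the active group is split equally (so three equal groups), compound symmetry, no dropout.

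**Formula.** G*Power, repeated measures, within-between interaction, k groups, m measurements: λ = N·f²·m/(1 − r), df1 = (k − 1)(m − 1), df2 = (N − k)(m − 1).

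**Step 1: reproduce the plan's figures.**
- App versus waiting list, k = 2, f = 0.25: N = 24 gives λ = 24 × 0.0625 × 3/0.4 = 11.25, df 2 and 44, power 0.835. This matches the stated 24.
- Small effect, k = 3, f = 0.10: N = 162 gives λ = 162 × 0.01 × 3/0.4 = 12.15, df 4 and 318, power 0.801. This matches the stated 162.
- Small effect, k = 2, f = 0.10: N = 130 gives λ = 9.75, df 2 and 256, power 0.800.

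Other inputs come close to 162 with two groups (160 with two measurements, 164 with r = 0.5), but each contradicts a stated input. With three measurements and r = 0.6, only k = 3 gives 162.

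**Step 2: rejection by the three-group test when SER and SSIP are identical.** Let the app effect build linearly: 0, d/2, d SD at t0, t1, t2. With one third on the waiting list, the between-group part is (1/3)(2/3) = 2/9 and the mean squared time deviation is d²/6. So f² = (2/9)(d²/6) = d²/27, and λ = N·(d²/27)·3/0.4 = N·d²/3.6.

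| App effect d (assumed) | f | Rejection, N = 162 | Rejection, N = 250 |
|---|---|---|---|
| 0.2 | 0.038 | 0.16 | 0.23 |
| 0.3 | 0.058 | 0.32 | 0.48 |
| 0.5 | 0.096 | 0.77 | 0.93 |

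Simulation (4,000 trials per setting) agrees. At about 83 per group, different versions of the omnibus test gave 23%, 47–50% and 92–93%, and about 5% with no app effect. With 30% loss the rates were 33% at 0.3 SD and 80% at 0.5 SD. At the protocol's own f = 0.25, rejection exceeds 0.999 at both sample sizes. Under this build-up, however, f = 0.25 means d = 0.25 × √27 = 1.30 SD, so the table is the more useful guide.

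**Step 3: the direct contrast.** The SER-first versus SSIP-first by time test rejected in 4.5–5.6% of simulated trials whatever the app effect. This held whether it was fitted in the active groups alone or as a contrast in the model with the waiting list.

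**Step 4: size of the direct contrast at f = 0.10.** 130 active participants means 130 × 1.5 = 195 in total. At 250 randomised, about 167 are active (λ = 12.5) and power is 0.89. At 162 in total, 108 are active (λ = 8.1) and power is 0.72.

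**The case against.** The strongest reply is that the analysis section does not name a three-level test. It names two components, never calls the waiting list a component, uses the separate word condition elsewhere, and deals with app versus control in an earlier sentence. The phrase about using all participants can mean intention-to-treat with incomplete cases kept, since the next sentence is about missing values. On that reading the planned test is already SER versus SSIP, and coding detail may be left to an analysis plan that is not shown. The 162 would then show only how a number was obtained.

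Much of this stands. A reader might infer that the protocol has committed itself to an omnibus test; the analysis section alone does not show that. A reader might also infer that keeping the waiting list in the model inflates the error rate. It does not, because the contrast holds 5% in the same model.

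The reply does not remove the point. The only test the document sizes for this objective is the three-group interaction, described as an effect "to detect a small effect between the two active conditions and the waitlist control group". Either that is the intended test, and it has the wrong null, or the two sections describe different tests. This is a mismatch within the published text and not merely omitted detail.

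It is also fair to object that comparing the groups at t1 only would drop the crossover's second period. That is one acceptable choice and not the only one.

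**Conclusion.** The point holds in this form: the protocol states no SER-minus-SSIP contrast, and the sample size behind the objective is a three-group omnibus interaction that includes the waiting list. If that interaction is used as the test, it cannot separate a component difference from an app effect. With identical components, its chance of significance at 250 randomised runs from about 23% at 0.2 SD to about 93% at 0.5 SD.

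Two stronger readings are not supported. The test does not reject whenever the app works; for small app effects it rejects in a minority of trials. Nor does the error in the 162 leave the component comparison underpowered at the planned size, since 250 gives about 0.89 before dropout.

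The rates rest on assumed app effects (the document gives none in SD units), a linear build-up, equal thirds and compound symmetry. They come from repeated-measures ANOVA and change-score tests, not from the planned mixed model with random slopes. This concerns a secondary objective. It should be corrected before analysis, and it does not affect the primary comparison.

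**What to change.** In Statistical analyses, state that the differential effect is the contrast between the SER-first and SSIP-first groups. This could be baseline-adjusted change to t1, or the two-sequence-by-time interaction if the crossover's second period is used. Add that the waiting list may stay in the model to help estimate time and variance but does not enter this contrast, and that a significant three-group interaction is not evidence of a component difference.

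In Sample size calculations, replace the 162 with the figure for the two-group by time contrast: 130 active participants, 195 in total at 1:2, with about 0.89 power at 250 randomised before dropout, assuming equal thirds. If t1 alone is chosen, recompute for that analysis. As a simple guide, 195/250 = 0.78, so about 22% loss brings the active groups down to 130.

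The cost is a few sentences and no new data. The downside is that the targeted contrast will be significant less often than the omnibus test.

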### Measures

#### Primary and secondary outcomes

All primary and secondary outcomes will be measured via online self-report questionnaires. Participants will be asked to complete them before the intervention (t0), 5 weeks after starting the intervention (t1, intermediate measurement), which will correspond to the time needed to complete the first component, and 11 weeks after starting the intervention (t2). By this time, participants will have completed both components of the intervention, which corresponds to the post-measurement. Furthermore, participants will be asked to complete the questionnaire again 11 weeks after finishing the FACE self-help app, which serves as a follow-up (t4). An exception is the adapted Patient Satisfaction Questionnaire, which will be assessed only after the finishing first component (t1), and after finishing the second component of the self-help app (t2). Reminders to fill out the questionnaire will be sent after 2 and 4 weeks.

***Resilience*** will be assessed with the 10-item German version [51] of the Connor-Davidson Resilience Scale (CD-RISC) [21], which has been shown to be a valid and reliable measurement [51, 52]. The CD-RISC is widely used and has been shown to be sensitive to change following interventions [21, 53]. The items are rated on a 5-point scale ranging from 0– Not true at all to 4– True nearly all the time.

***Well-being*** will be assessed with the Warwick-Edinburgh Mental Well-being Scale (WEMWBS) [54]. The German version of the scale shows good reliability and validity [55]. The scale contains 14 items that are rated on a 5-point scale ranging from 1– never to 4– always.

***Self-efficacy for managing emotions*** will be assessed with the PROMIS Short Form v1.0 - Self-Efficacy for Managing Emotions [56]. PROMIS items were developed for use in the general population for different aspects of mental health. Method and assessment timepoint: The scale contains 7 items that are rated on a 5-point scale ranging from 1– never to 4– always.

***Fear of negative evaluation*** will be assessed with the German short version of the Fear of Negative Evaluation Scale (SANB-5) [57]. The scale contains 5 items that are rated on a 4-point Likert scale from 1 - almost never true to 4- almost always true.

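### The SER-versus-SSIP test leaves the coding of time and the deciding visit open, although the crossover separates the components only up to t1

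*Protocol article*

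**What the plan says.** Under Statistical analyses, the article first plans linear mixed models for intervention against waiting list. On the components it says: "The differential effects of the SER and SSIP components will then be tested with interactions between the component and time". It continues: "These analyses will model random slopes and intercepts for participants". The fixed effects are given as condition and the repeated assessments over time. The coding of time is not stated. Nor is it stated whether component means the randomised sequence or the component most recently received.

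The Trial design section describes a crossover of the two components within the active group. Under Primary and secondary outcomes, t1 falls at week 5, after the first component, and t2 at week 11. Of t2 the article says: "By this time, participants will have completed both components of the intervention".

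The Secondary objectives expect each component to do more for its own target variables than the other component does. The Exploratory objectives ask a separate question: whether the order of the components affects the outcome.

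**The concern.** The information on SER against SSIP lies mainly at t1, when each active sequence has had exactly one component. At t2 the two sequences have had the same content in a different order, so a difference there speaks to order rather than to component. A bare component-by-time interaction does not say which of these it targets.

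Two readings of the text lead to very different tests. If time enters as a straight line, the interaction compares slopes, and a slope over three visits gives the middle visit almost no weight. If time enters as a factor, the test sees t1, but it pools t1 and t2 into one joint result. The differential effect is a stated secondary objective and the reason given for splitting the active group. Under the first reading, a real component difference would probably be reported as absent. Under the second, a significant result would not show whether component or order produced it.

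**Working it through.** **Inputs from the article.** Test level: "The significance level will be two-sided at *p* ≤ 0.05". Sample size settings: "with a power of 0.8, an alpha error of 0.05". Component effect: "a small effect of *f* > 0.10 for the differential effects between SER and SSIP". Main effect: "We expect a moderate effect size of *f* > 0.25". Correlation: "we expect a correlation between the pre- and post-measurement of *r* = 0.6". Visits fall at weeks 0, 5 and 11. Up to 250 participants are randomised, 1:2 control to intervention, so about 167 are in the active group.

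**Assumptions added here.** An equal split of the active group (83 and 84), SD of 1 at each visit, the same correlation between all pairs of visits, no dropout.

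**Step 1: the article's own figures.** For a repeated-measures within-between interaction with k groups and m measurements, the noncentrality is λ = f²·N·m/(1 − r), with (k − 1)(m − 1) and (N − k)(m − 1) degrees of freedom.
- f = 0.25, k = 2, m = 3, N = 24: λ = 0.0625 × 24 × 3/0.4 = 11.25; power 0.835.
- f = 0.10, k = 3, m = 3, N = 162: λ = 0.01 × 162 × 3/0.4 = 12.15; power 0.801.

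Both stated sample sizes reproduce. This calculation treats time as a factor with three levels, not as a line.

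**Step 2: the expected pattern.** If component effects are additive and lasting, the difference between sequences on a target variable is (0, d, 0) at t0, t1 and t2. For two equal groups, f² = (1/3) × (2d²/3)/4 = d²/18. So f = 0.10 corresponds to d = 0.10 × √18 = 0.424 SD at t1. Applying f = 0.10 to the two active sequences alone is an assumption, since the 162 was computed with three groups.

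**Step 3: linear time.** Centred weeks are −5.33, −0.33 and 5.67, with sum of squares 60.67.
- Expected slope difference: −0.33 × 0.424/60.67 = −0.0023 per week, slightly in the wrong direction.
- Standard error: √(0.4/60.67 × (1/83 + 1/84)) = 0.0126.
- Power: 0.054. With time coded 0, 1, 2 the t1 weight is exactly zero and power is 0.050. At d = 0.2 with time in weeks it is 0.051.

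Extra random-slope variance would change the standard error but not the near-zero expected value.

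**Step 4: linear time if the sequences do not meet at t2** (d = 0.424 at t1).

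| Difference at t2 | Power of slope test |
|---|---|
| half of the t1 difference remains | 0.28 |
| reverses by half | 0.42 |
| remains in full | 0.84 |
| reverses in full | 0.91 |

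The gain comes from the t2 difference, that is, from the order question.

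**Step 5: categorical time, interaction on 2 degrees of freedom.** λ = (2d²/3)/(0.4 × (1/83 + 1/84)) = 0.12/(0.4 × 0.02395) = 12.5; power 0.894. At d = 0.40 it is 0.85.

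**Step 6: a named contrast at t1.**
- Change from t0 to t1: standard error √(2 × 0.4 × 0.02395) = 0.138; power 0.861 at d = 0.424.
- Baseline-adjusted difference at t1: standard error √((1 − 0.6²) × 0.02395) = 0.124; power 0.93 at d = 0.424, about 0.89 at 0.40 and about 0.67 at 0.30.

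**The case against.** The strongest reply is that the 5% belongs to a model the article never specifies. A reader might infer from the random slopes that mean change is linear. That does not follow: a random slope puts a linear term in the random part only, and visit can still be a factor in the fixed part. The separate mention of repeated assessments as fixed effects, and a power calculation that reproduces only with time as a factor, both fit categorical time. On that reading the test is not weak.

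A reader might also infer that the model cannot be fitted, because random intercept, random slope, their covariance and a residual are four parameters against three distinct variances and covariances when only t0 and t1 are used. Nothing in the article limits the model to those two visits; it plans three measurements and a follow-up.

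Further, exact meeting at t2 is an inference. The Exploratory objectives leave open that one order does better. Component could also mean the component just received. Finally, time coding and contrasts may sit in an analysis plan that is not shown.

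Most of this stands, and it limits the point. What it does not remove is that the stated model admits the weak linear reading, and that even the favourable categorical reading combines the component and order questions in one test.

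**Conclusion.** The point holds as a conditional one. The article fixes a component-by-time interaction with random participant slopes, but leaves open the choice on which its power and meaning depend. With linear time and sequences that meet at t2, power is about 5%. With categorical time it is about 0.89 at f = 0.10, so the objective is not lost, but the joint test does not separate the t1 component difference from the t2 sequence difference. A baseline-adjusted t1 contrast gives about 0.93 and answers the component question directly.

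The figures rest on an equal split of 167 active participants, a uniform correlation of 0.6, no dropout, and f = 0.10 read as a t1 difference of 0.424 SD between the two sequences. Dropout would lower all the useful power values. The documents do not show that the planned model is linear or that it would fail to fit. This is a worthwhile and cheap clarification, not evidence that the planned analysis is invalid.

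**What to change.** State in the analysis section that visit is categorical in the fixed part. An unstructured within-person covariance is one suitable choice in place of random slopes; with three visits it has six parameters. Name the baseline-adjusted difference between the SER-first and SSIP-first sequences at t1 as the test of differential component effects, and define component in that test as the one received in the first period. Assign the difference between sequences at t2 to the exploratory question on order.

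The cost is wording and model syntax. Sample size, visits and data collection do not change.
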